### Rationale: choice of comparators

In France, total thyroidectomy with prophylactic central compartment (level VI) neck dissection as defined by the American Thyroid Association [38] is standard treatment recommended by the French Society of Otolaryngology Head and Neck Surgery,[15] whereas total thyroidectomy alone without neck dissection is recommended as standard treatment by the Francophone Association of Endocrine Surgery [19].

A simulation by the American Thyroid Association, hypothesizing a 25% difference in significant oncologic events at 7 years, with a statistical power of 80%, concluded that a randomized trial was “not readily feasible” due to the need to randomize 5840 patients [39]. This implies that both therapeutic strategies may indeed be equivalent within a small percentage, and we have therefore designed our study with a *non-inferiority statistical design with a surrogate endpoint*. This methodology (non-inferiority trial) has been clearly validated in these low-risk patients by two previous studies carried out by the same French thyroid network (TuThyRef) and published in the New England Journal of Medicine, ESTIMABL[40] and ESTIMABL2 [41]. The surrogate endpoint in the present study is the rate of excellent response as defined by the ATA,[13] or complete remission, at 1 year.

If our study confirms the non-inferiority of total thyroidectomy alone, prophylactic central compartment neck dissection could be abandoned for these low-risk patients without taking undue oncologic risks. Secondary endpoints may also show a benefit in terms of patient quality of life and of cost-utility analysis with a total thyroidectomy alone. Patients, physicians, and healthcare providers would all benefit from less-extensive surgery.

### Objectives

#### Primary objective

To assess the non-inferiority of total thyroidectomy alone as compared to total thyroidectomy with bilateral prophylactic central compartment neck dissection in terms of the rate of complete remission (excellent response) at 1 year after randomization, for differentiated thyroid cancer cT1bT2N0. We hypothesize that the rate of complete remission after thyroidectomy alone is not inferior to the rate of complete remission after thyroidectomy with PND by more than 5% at 1 year.

The primary criterion is the rate of patients *in complete remission* (excellent response) at 1 year after randomization (8+/2 months post-^131^I) as defined by the presence of all 3 criteria:Normal whole body scan (SPECT-CT) performed after the administration of 30 mCi (1.1 GBq) of 131I administered within 2–4 months following surgery,Normal neck ultrasound 8+/−2 months after the ^131^IUnstimulated ultrasensitive thyroglobulin while on L-thyroxine treatment (usTg/LT4) ≤ 0.2 ng/mL) without anti-Tg antibodies (TgAb) 8+/−2 months after administration of ^131^I

In this network’s previous study, 94% of the low-risk patients (including 12% T2N0) were in complete remission 1 year after surgery and administration of 131I after rhTSH [40]. In a similar prospective multicentre trial, 90.2% of the low-risk patients, including patients T1–T3 N0–N1 with or without central compartment neck dissection, were in complete remission 1 year after surgery and administration of 131I after rhTSH [42]. For low-risk patients showing an excellent response after treatment, the risk of recurrence is estimated to be 2–3% [4].

#### Secondary objectives

To compare total thyroidectomy and radioactive iodine (^131^I) to total thyroidectomy with bilateral prophylactic central compartment neck dissection and 131I in terms of:Thyroglobulin levels after surgery alone (usTg/T4) measured while on T4 treatment, 8+/−2 weeks postoperatively, before stimulation and administration of radioactive iodinePercent of patients in complete remission (excellent response) at 3 and 5 years after randomization, as defined by a normal neck ultrasound and usTg/LT4 ≤ 0.2 ng/m. The endpoint of 5 years reflects the data from a prospective multicenter study of 715 patients reporting that 81% of recurrences occurred within 5 years,[43] and from a retrospective study of 1020 patients followed for 10 years reporting that all structural recurrences occurred within 8 years, with 77% occurring within 5 years [44].Percent of patients at 1, 3, and 5 years after randomization with structural incomplete response in the neck defined by a malignant lesion in the neck detected by ultrasound and confirmed by cytology (and/or Tg in the needle washout fluid >10ng/ml). Cytology will be mandatory for suspicious lesions measuring 8mm or more in the smallest diameter; lesions with suspicious features on ultrasound but measuring <8 mm may undergo cytology at the discretion of the center’s principal investigators.Percent of patients at 1, 3, and 5 years after randomization with biological incomplete response defined by a normal neck ultrasound and absence of disease detected on other conventional or metabolic imaging (^131^I, ^18^FDG-TEP), if performed, associated with a serum Tg/LT4>0.2 ng/mlPercent of patients at 1, 3, and 5 years after randomization with an indeterminate response defined by a suspicious lesion on neck ultrasound without cytological proof of disease and/or detection of TgAbPercent of patients at 1, 3, and 5 years after randomization with diagnosis of distant metastases on metabolic imaging (^131^I, ^18^FDG-TEP) or cross-sectional imaging, and confirmed cytologically (except for metastases with ^131^I uptake) or with repeat imaging at 6 months (if cytology not possible)Percent of patients at 1, 3, and 5 years after randomization having undergone further treatment (surgery or 2nd therapeutic administration of ^131^I, number of retreatments per patient and indication for each retreatment)At 1 year: percent of patients with persistent hypoparathyroidism with supplementation and/or persistent vocal fold paralysis; subjective dysphonia (Voice Handicap Index)[45] and dysphagia (SWAL-QOL)[46] (questionnaires in their validated French versions) compared between groups after randomization: Quality of life SF36[47], EuroQol EQ-5D,[48] Anxiety (State-Trait Anxiety Inventory-STAI)[49]Cost-utility analysis.

### Trial design

Prospective randomized open phase III non-inferiority trial in patients with cT1bT2N0 [50] papillary thyroid carcinoma comparing: total thyroidectomy alone (experimental group) versus total thyroidectomy with prophylactic neck dissection (PND) (reference group).

*Group 1 (reference group)*: total thyroidectomy with bilateral prophylactic central compartment (level VI) neck dissection

*Group 2 (“experimental” group)*: total thyroidectomy alone without neck dissection.

Before surgery, the patients will first be pre-registered (included) to check that the thyroid nodule is classified cT1bT2N0 and the FNAB cytology is classified type 5 or 6 according to the Bethesda classification [51].

Surgery must be performed within 4 months of inclusion.For patients with *FNAB cytology Bethesda 6 “papillary carcinoma”*, inclusion and randomization will we performed preoperatively.For patients with *FNAB cytology Bethesda 5 “suspicious cytology”*, randomization (and validation of the inclusion) will then be performed in the operating room, after confirmation of malignancy by intra-operative frozen section analysis. For these patients, randomization will be performed online or by fax with the Trial Master program.

All patients will have Tg/LT4 measured 8 +/−2 weeks postoperatively, *before stimulation with recombinant human thyrotropin (rhTSH).*

All patients will receive, 2–4 months postoperatively, 30 mCi (1.1 GBq) ^131^I after stimulation with human recombinant thyrotropin (rhTSH) and undergo scintiscan with SPECT-CT. Neck ultrasound will be performed at the time of ^131^I administration (standard of care).

Patients will be evaluated at 8 +/−2 months post-iodine (8–14 months postoperatively or “1 year”) then yearly with neck ultrasound, unstimulated ultrasensitive thyroglobulin (usTg/LT4), and anti-Tg antibodies.

## Methods: participants, interventions, and outcomes

### Study setting

This is a multicenter study involving only specialized university hospitals and comphrehensive cancer centers in France. The list of study sites can be obtained by contacting the principal investigator or data manager at Gustave Roussy.

### Eligibility criteria

#### Inclusion criteria

Thyroid nodule measuring *11–40 mm* on ultrasound (*cT1bT2*)AND with fine-needle aspiration biopsy (FNAB) cytology in favor of “papillary thyroid carcinoma” (*Type 6 according* to the Bethesda classification (Appendix 2)
*OR* with FNAB cytology “suspicious for malignancy” (*Type 5* according to the Bethesda classification). In this latter case, randomization will be performed if confirmation of papillary carcinoma on intra-operative frozen section analysiscN0: absence of lymph nodes suspicious for malignancy on preoperative ultrasound performed by the center’s designated radiologists according to a standardized report[52]Absence of a medical contraindication to performing a total thyroidectomy with or without bilateral prophylactic neck dissection of the central compartmentWomen of childbearing potential should have a negative pregnancy test (serum or urine) before any radioiodine administration. Sexually active patients must agree to use an effective method of contraception or to abstain from sexual activity during the study and for at least 6 months after last dose of radioiodine.Patient affiliated to a social security regimen or beneficiary of such regimenPatients age ≥ 18 years old, French-speakingPatients should understand, sign, and date the written informed consent form prior to any protocol-specific procedures. Patients should be able and willing to comply with study visits.

#### Non-inclusion criteria

Tumors > 40 mm (cT3) or ≤ 10 mmTumors with extrathyroidal extension suspected or obvious on the preoperative work-up or intra-operatively (cT3T4)Metastatic neck lymph nodes or suspicious neck nodes on preoperative ultrasound (cN1); for suspicious nodes, FNAB cytology and thyroglobulin assay on the needle washout fluid will be performedMetastatic neck lymph nodes found during the thyroidectomy and confirmed with intra-operative frozen section analysisMedullary thyroid carcinoma on FNAB cytology and/or with basal serum calcitonin >50 pg/mlPreoperative or intra-operative suspicion of non-papillary thyroid carcinoma or aggressive histopathological subtype or poorly differentiated carcinomaDistant metastases (M1) apparent preoperatively (found due to symptoms or fortuitously; no specific preoperative work-up will be performed, however, in accordance with current clinical practice)Recurrent nerve paralysis visualized on systematic preoperative laryngoscopy and/or abnormal preoperative serum calciumPregnant or breast feeding womenParticipation in another therapeutic clinical trial within 1 year from study entryPatient under guardianship or deprived of their liberty by a judicial or administrative decision or incapable of giving their consent

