### Intervention description

#### Randomization of patients

*Pre-registration (inclusion)* of eligible patients after signed informed consent.Surgery must be performed within 4 months of pre-registration.Quality of life (SF-36, EQ-5D, STAI) questionnaires will be completed by the patient within 1 month before the surgery.Before surgery, the patients will first be pre-registered (included) to check that the thyroid nodule is classified cT1bT2N0 and the FNAB cytology is classified type 5 or 6 according Bethesda (Appendix 2).Randomization (and validation of the inclusion)

Randomization (and validation of the inclusion) will then be performed:Before surgery for patients with malignant cytology (Bethesda 6)OR in the operating room, after total thyroidectomy without any particular dissection of paratracheal spaces and after confirmation of malignancy by intra-operative frozen section analysis for patients with suspicious cytology (Bethesda 5).

For patients with a nodule Bethesda 5, the randomization form will incude a confirmation of malignancy of the intra-operative frozen section analysis for patients with suspicious cytology Figs. 1 and 2.

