### Criteria for discontinuing or modifying allocated interventions

Secondary exclusion will be performed for patients in whom final pathology (non-frozen section analysis but defintive pathological evaluation) does not confirm the presence of a differentiated thyroid cancer.

In no other instances does this study provide for discontinuing or modifying allocated interventions.

Reasons for withdrawal from the trial (study interventions and follow-up) may include:Lost to follow-upWithdrawal of consentDeath

If a patient does not return for a scheduled visit, every effort will be made to contact them. In any case, every effort will be made to document the patient outcome and all attemps should be documented in the corresponding medical file. The investigator will inquire about the reason for withdrawal, request the patient to return for a final visit, if applicable, and follow up with the patient regarding any unresolved adverse events. The early termination final visit should include all assessments listed for the End of Study visit.

If the patient withdraws their consent for the study, no further study-specific evaluations will be performed, and no additional data will be collected. The sponsor may retain and continue to use any data and samples collected before such refusal except in case of patient opposition. Any opposition will be transmitted by the investigator to the sponsor without undue delay.

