## Assignment of interventions: allocation

### Sequence generation

Patients will be prospectively included in the study in 2 steps:Patients will first be registered, after check of eligibility criteria and signature of the informed consent form, before any trial related procedure.Randomization (and validation of the inclusion) will then be performed: (1) before surgery for patients with malignant cytology (Bethesda 6) or (2) in the operating room, after total thyroidectomy and after confirmation of malignancy by intra-operative frozen section analysis for patients with suspicious cytology (Bethesda 5). Randomization will be performed online or by fax with the Trial Master program.

Randomization will be performed online or by fax with the Trial Master program. Patients will be randomly allocated to one of the two treatment groups, based on blocks of participants, stratified by tumor size (cT1b vs cT2) and site (to ensure a balance between the treatment groups at each site). The blocking and stratification measures will not be revealed to those enrolling patients or those allocating the interventions.

Once randomized, patients must be treated as defined in the assigned group and cannot change.

Inclusion/registration and randomization will be performed online or by fax, using the TrialMaster program, and electronically centralized by the Biostatistics and Epidemiology Unit at Gustave Roussy. A fax or an internet access in the operating room or at proximity is then mandatory. In case of any kind of problem, the investigator will contact the study data manager.

The data manager email address, phone, and fax number will be notified in the CRF. In case of any emergency or in the absence of the study data manager, an on-duty data manager will available.

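### The intra-operative non-inclusion criteria are not limited to findings before randomisation, so in Bethesda 6 patients they would act as post-randomisation exclusions that the protocol does not provide for

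*Protocol article*

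**What the plan says.** **Eligibility.** The Non-inclusion criteria contain three items that can be met at operation:

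- metastatic "lymph nodes found during the thyroidectomy and confirmed with intra-operative frozen section" analysis;
- extrathyroidal extension seen before or during surgery;
- suspicion, before or during surgery, of a non-papillary, aggressive or poorly differentiated tumour.

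No item is restricted by cytology class or by the time of randomisation.

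**Timing of randomisation.** For Bethesda 6, Trial design says "inclusion and randomization will we performed preoperatively". Randomization of patients and Sequence generation agree. For Bethesda 5, allocation takes place "in the operating room, after total thyroidectomy without any particular dissection of paratracheal spaces" and after frozen section has confirmed malignancy. The Inclusion criteria say the same: "In this latter case, randomization will be performed if confirmation of papillary carcinoma on intra-operative frozen section".

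**After randomisation.** Criteria for discontinuing or modifying allocated interventions gives one ground for removal: "Secondary exclusion will be performed for patients in whom final pathology" does not confirm differentiated cancer. It adds: "In no other instances does this study provide for discontinuing or modifying allocated interventions". Sequence generation states: "Once randomized, patients must be treated as defined in the assigned group and cannot change".

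**Analysis.** Statistical methods makes the per-protocol (evaluable) population primary and ITT a sensitivity analysis. Evaluable means treatment and follow-up that conform to the protocol, and no detectable anti-Tg antibodies.

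**The concern.** For a Bethesda 6 patient, everything found at surgery is found after allocation. A surgeon who sees a frozen-section-positive node in such a patient meets a listed non-inclusion criterion in plain words. Yet the section on discontinuing interventions gives no route to exclude her.

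In Bethesda 5 the protocol keeps detection equal between arms, because randomisation follows a thyroidectomy in which the paratracheal spaces are not specifically dissected. Bethesda 6 has no such safeguard. The surgeon knows the arm from the outset, two of the three criteria turn on suspicion, and only the dissection arm goes on to open the central compartment. Removals could therefore differ by arm, and they would act directly on the primary per-protocol comparison.

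**Working it through.** **1. The rules side by side, for a Bethesda 6 patient with a listed finding at surgery**

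| Section | What it implies |
|---|---|
| Non-inclusion criteria | Taken literally, not eligible |
| Trial design; Randomization of patients; Sequence generation | Already randomised |
| Criteria for discontinuing or modifying allocated interventions | No exclusion unless final pathology is not differentiated cancer |
| Sequence generation | Assigned operation must be given |
| Statistical methods | Evaluable if treated as allocated, followed up and free of anti-Tg antibodies |
| Determination of sample size | 5% allowance, for final histopathology only |

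The first row is out of line with the third. It is out of line with the fourth only if the finding changes the operation. No text shown says which row governs; the trial-design and randomisation diagrams are not available.

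**2. The plan's own sample size**

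With equal remission rate p in both arms, margin 0.05, one-sided alpha 0.025 and power 80%: n per arm = (1.960 + 0.842)² × 2p(1 − p) / 0.05². At p = 0.95 this gives 299, as stated. The 95% is inferred, because the document states no design rate; its cited 94% and 90.2% would give 355 and 556. The 628 to be randomised is 598 × 1.05.

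**3. Shift in one arm's rate if patients are removed from it**

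Inputs: 299 per arm and base rate b = 0.94 (both from Determination of sample size). The number removed k and their remission rate r are assumptions. With f = k/299, shift = (b − f·r)/(1 − f) − b.

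| Net removal from one arm | r = 0.94 | r = 0.80 | r = 0.50 | r = 0 |
|---|---|---|---|---|
| 3 of 299 (1%) | 0 | +0.14 | +0.45 | +0.95 |
| 9 of 299 (3%) | 0 | +0.43 | +1.37 | +2.92 |

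Entries are percentage points, against a margin of 5. With b = 0.902 the ranges are 0 to 0.91 (k = 3, r from 0.902 to 0) and 0 to 2.80 (k = 9). Removing poor responders from the thyroidectomy-alone arm favours non-inferiority; removing them from the dissection arm works against it. Equal removal of similar patients largely cancels.

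**4. Power if the patients are kept**

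Power = Φ(0.05/√(2p(1 − p)/n) − 1.960), at the inferred 95% for other patients and an assumed 80% for those with findings. With 299 per arm and no such patients, power is 80.1%.

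| Share of each arm | Kept: rate, power (n = 299) | Removed: n per arm, power |
|---|---|---|
| 1% | 0.99 × 0.95 + 0.01 × 0.80 = 0.9485, 79.0% | 296, 79.7% |
| 3% | 0.97 × 0.95 + 0.03 × 0.80 = 0.9455, 76.8% | 290, 78.9% |

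**The case against.** The case for the benign reading is good. The list is headed as criteria for non-inclusion, and the protocol describes randomisation as the step at which inclusion is also validated. Eligibility should therefore close there, after which the secondary-exclusion and treat-as-assigned rules govern. The only frozen section that the text requires is in Bethesda 5. Under Statistical methods as written, a patient treated as allocated and followed up stays evaluable, so harm arises only if a site applies the list after allocation. ITT is also planned.

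Most of this stands and limits the weight of the point. It does not remove it: the intra-operative wording is unrestricted, and nothing shown tells a site that the list no longer applies once a Bethesda 6 patient is allocated. Eligibility and exclusion are protocol matters, and here the stated rules do not fit together.

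A reader might go further in three ways that the documents do not support:

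- **That the list always breaches the treat-as-assigned rule.** That rule concerns the operation given. Dropping a patient after she has received her assigned operation does not break it.
- **That detection differs by arm for all three criteria.** Opening the central compartment bears mainly on nodes. The other two concern the primary tumour, which is removed in both arms. Even the node item speaks of nodes found during thyroidectomy, which both arms undergo.
- **That patients with positive nodes or risk factors on final pathology are to be removed.** Explanation for the choice of comparators records metastatic nodes as data, and the Discussion expects patients with intermediate risk factors to be included.

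**Conclusion.** The point holds as a minor inconsistency in the rules. Applied literally to Bethesda 6 patients, the intra-operative criteria are a post-randomisation exclusion that the protocol does not provide for, decided by surgeons who know the arm and acting on the per-protocol primary analysis.

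A reader might infer that the primary result is biased, or biased towards non-inferiority. The documents do not support that. They give no Bethesda 6 share, no frequency of such findings and no remission rate for these patients, and they do not show that any patient has been removed this way. The shifts of 0 to 0.95 points (1% net removal) and 0 to 2.92 points (3%) are illustrations; the upper ends require that none of the removed patients remits. ITT is a partial safeguard.

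**What to change.** - **Non-inclusion criteria:** state that the intra-operative items apply only to findings made before randomisation, in practice in Bethesda 5.
- **Criteria for discontinuing or modifying allocated interventions, and the two sections defining evaluable patients:** state that a randomised Bethesda 6 patient with such a finding is not excluded on that ground, is followed to 1 year, and is analysed in her randomised arm in ITT and, if treated as allocated and otherwise evaluable, in the primary analysis.
- **Reporting:** give by arm the number of such findings and the number of thyroidectomy-alone patients dissected because of them. The latter still leave the per-protocol set as treatment deviations, while a dissection-arm patient with the same nodes stays. The wording change does not cure that asymmetry; for these patients the ITT result is the safeguard.

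The cost is a clause and a few sentences, with ethics committee approval. Randomisation, treatment and visits do not change. Accrual began in August 2018, so sites should check whether any Bethesda 6 patient has already been removed on these grounds and complete the 1-year data where consent allows.

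The downside is that a few higher-risk patients stay in the analysis. Under the assumptions above, at 1% of each arm the expected rate falls by 0.15 points and power is 79.0% rather than 79.7% with them removed; at 3% it falls by 0.45 points and power is 76.8% rather than 78.9%.
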